##### Immunogenicity Analysis

The primary endpoints of the immunogenicity analysis will focus on quantifying and comparing immune responses elicited by the vaccine across study groups and time points. The seroconversion rate will be determined as the proportion of participants who achieved a predefined antibody threshold postvaccination relative to their baseline levels, indicating the vaccine’s ability to induce a measurable immune response. In addition, GMTs for antibody concentrations or the mean fluorescence intensity for flow cytometry–based assays will be calculated to summarize central tendencies of immune responses while minimizing the influence of extreme values. These parameters will be statistically compared across treatment arms, dose groups, and time points via appropriate statistical tests such as paired 2-tailed *t* tests, Wilcoxon signed-rank tests, or one-way ANOVA, depending on the data distribution. Additionally, to assess immune kinetics, longitudinal models, which describe patterns of immune waning or boosting following primary and subsequent vaccine doses, will be used. Furthermore, correlation analyses, including protection against infection during the entire study period, will be performed to explore the relationship between antibody levels and clinical outcomes, thereby identifying potential immunological correlates of protection and revealing the predictive value of measured immune parameters.

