##### Secondary End Points: Immunogenicity End Points

The secondary end points are (1) the proportion of participants with a specific TANCoV-1.3.20 humoral response, (2) the magnitude of the specific cellular response to TANCoV-1.3.20, (3) the proportion of participants with serum-neutralizing antibody responses to TANCoV-1.3.20, and (4) the characteristics of the humoral response produced by the TANCoV-1.3.20 vaccine.

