### Sample Size Estimation

The sample size for this noninferiority clinical trial was calculated to compare the proportion of seroconversion on day 28 between participants receiving the investigational vaccine TANCoV-1.3.20 and those receiving the standard Sinopharm COVID-19 vaccine. On the basis of prior studies and seroconversion data from the Tanzanian setting, we assumed an 88% seroconversion rate for the control group (Sinopharm) and expected a 90% seroconversion rate in the experimental group. A noninferiority margin of 20 percentage points was set, meaning that TANCoV-1.3.20 would be considered noninferior if its seroconversion rate was not more than 20% lower than that of Sinopharm. Using a 1-sided significance level (α) of .05, 80% power (1−β), and a 1:1 allocation ratio (experimental: control), the required total sample size was estimated at 50 participants per group. The study includes 3 study groups, with 25 participants per arm, resulting in a total planned sample size of 150 participants. This sample size provides sufficient power to establish noninferiority if the lower bound of the CI for the difference in seroconversion remains above the preset margin. The calculation assumes binomial proportions and follows standard methods for noninferiority designs in parallel trials [30].

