#### Immunogenicity Assessment

The processed samples (sera) will be analyzed to evaluate immunoglobulin G (IgG) and immunoglobulin M (IgM) titers using the WANTAI SARS-CoV-2 Ab enzyme-linked immunosorbent assay. The resulting antibody concentrations will be quantified, and the values will be expressed as GMTs to provide a reliable summary measure of the immune response while minimizing the effect of extreme values or outliers.

In addition to humoral responses, the cell-mediated immune response will be characterized to provide insights into T-cell activation and cytokine production following vaccination. This will include an interferon-γ (IFN-γ) enzyme-linked immunospot assay to quantify antigen-specific T-cell responses, alongside an intracellular cytokine staining assay performed on cryopreserved PBMCs. The intracellular cytokine staining assay allows detailed profiling of cytokines such as IFN-γ, interleukin-2 (IL-2), tumor necrosis factor-α (TNF-α), and other relevant markers, enabling the evaluation of T-cell subsets (cluster of differentiation 4 [CD4^+^] and cluster of differentiation 8 [CD8^+^]) involved in vaccine-induced immunity.

All immunology work and long-term sample storage, for at least 15 years, will be centralized at the NIMR-Mbeya Center.

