#### Data Analysis

The data will be analyzed using Stata (version 14; StataCorp LLC). Findings will be reported according to the CONSORT (Consolidated Standards of Reporting Trials) guidelines. Primary analyses will be based on the intention-to-treat population, and secondary analyses will be based on the per-protocol population.

The primary end point will be analyzed via a marginal Poisson regression model fitted using generalized estimating equations, with the logarithm of follow-up time included as an offset and the study arm as the predictor. The incidence rate ratio and its 95% CI will be derived from the Poisson regression model. Incidence rates will also be calculated as the number of incident cases divided by the person-time in years, with person-time calculated from randomization to (1) the study end at 6 months after the last participant enrollment and (2) death or the time last seen if lost to follow-up. In addition, absolute effects on the primary endpoint will be summarized using risk differences (events per 1000 person-years) and their 95% CIs, estimated from the model-based predicted rates in each arm.

In a secondary analysis of the primary end point, we will adjust the Poisson regression model for covariates, defined a priori (age and sex). Each protocol analysis will be performed and defined according to reported adherence to the intended allocation. Subgroup analysis of the primary end point will also be performed via the Poisson model on the prespecified subgroup variables (age and sex).

Other secondary outcomes will be analyzed using generalized linear models, depending on their distributions. The mean difference with its 95% CI will be derived for a continuous outcome, and the odds ratio with its 95% CI will be estimated for a binary outcome.

AEs will be summarized according to the number and percentage of individuals experiencing AEs.

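### For flow cytometry the plan compares only mean fluorescence intensity, which does not count responding T cells and so can miss a real difference in the size of the cellular response

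*Protocol article*

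**What the plan says.** Three sections of the protocol article bear on the cellular response.

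- **End point.** Secondary End Points: Immunogenicity End Points lists "the magnitude of the specific cellular response to TANCoV-1.3.20". It names no assay.
- **Assays.** Immunogenicity Assessment plans an IFN-γ "enzyme-linked immunospot assay to quantify antigen-specific T-cell responses, alongside an intracellular cytokine staining assay performed on cryopreserved PBMCs". The staining assay is to profile cytokines and evaluate CD4+ and CD8+ subsets.
- **Analysis.** Immunogenicity Analysis names the seroconversion rate and then "GMTs for antibody concentrations or the mean fluorescence intensity for flow cytometry" assays. It continues: "These parameters will be statistically compared across treatment arms, dose groups, and time points".

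A general line in Data Analysis also applies: "Other secondary outcomes will be analyzed using generalized linear models, depending on their distributions". It gives a mean difference for continuous outcomes and names no cell-assay variable.

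**The concern.** Intracellular cytokine staining is read by flow cytometry, so the summary named for flow-based assays is the one that applies to it. That summary is an average brightness. The size of a T-cell response is usually understood as the number or share of cells that respond to the antigen, and brightness need not change when that share does.

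Objective 4 of the trial is to compare immunogenicity between the dose and booster regimens. If the staining data enter that comparison only as intensity, two arms with clearly different numbers of responding cells could look alike because of the variable chosen.

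**Working it through.** **1. The plan's own figure.** The only calculated figure is the sample size for noninferiority of seroconversion: 88% control, 90% experimental, margin 20 points, one-sided 0.05, power 80%.

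n per arm = (1.645 + 0.842)² × (0.88 × 0.12 + 0.90 × 0.10) / (0.02 + 0.20)² = 6.18 × 0.1956 / 0.0484 ≈ 25.

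This reproduces the plan: "The study includes 3 study groups, with 25 participants per arm". It supplies the arm size used in step 4. It says nothing about the cellular end point, for which the article gives no effect size or variability.

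**2. Intensity against frequency.** All values here are assumptions for illustration. Let f be the share of cells that respond, background intensity 1, and intensity of a responding cell k, with k the same in both arms.

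- Gated positive cells: the intensity ratio is k / k = 1.0, whatever the two frequencies are.
- All cells: mean intensity = 1 + (k − 1) × f.

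| Responding cells | Frequency ratio | All-cell ratio, k = 10 | All-cell ratio, k = 50 |
|---|---|---|---|
| 0.05% v 0.15% | 3.0 | 1.0135 / 1.0045 = 1.009 | 1.0735 / 1.0245 = 1.048 |
| 0.5% v 1.5% | 3.0 | 1.135 / 1.045 = 1.086 | 1.735 / 1.245 = 1.394 |

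**3. When the loss shrinks.** The second row shows that all-cell intensity moves more when responders are common. If brightness per responding cell rises by a factor r in the arm with more responders, the gated ratio becomes r rather than 1.0.

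**4. What this could mean for a comparison of 25 v 25.** Again for an assumed threefold difference, with a two-sided test at 0.05.

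On log10 frequency, the difference is log10(3) = 0.477. Power = Φ(0.477 / (SD × √(2/25)) − 1.96). For an assumed between-participant SD of 0.4, 0.5, 0.6 and 0.7 log10, this gives 99%, 92%, 80% and 67%.

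A simulation compared the three possible summaries by t test on log values (2,000 runs per setting). It assumed equal brightness in both arms, positive cells 20 times background, 100,000 cells per sample, and a between-participant SD of 0.2 on the natural-log scale for both positive and background intensity. Frequency SDs were 0.4, 0.5 and 0.7 log10.

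| Summary compared | Control responders 0.05% to 0.1% | Control responders 0.5% |
|---|---|---|
| Log frequency of positive cells | 64% to 98% | 66% to 98% |
| Intensity, gated positive cells | about 5% | about 5% |
| Intensity, all cells | 8% to 19% | 47% to 77% |

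The 5% for gated cells is the false-positive rate, and it follows directly from assuming equal brightness.

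**The case against.** **ELISpot.** A reader might infer that the analysis section contradicts the ELISpot measurement or leaves the end point without a usable analysis. The document does not support that. Fluorescence intensity is tied there to flow-based assays, and ELISpot is not one, so the section is silent on it. The generalized linear models of Data Analysis can take a spot count or a percentage of positive cells. The exact ELISpot summary is also detail that an article commonly leaves to the full protocol or SAP. This part of the objection stands. Intensity is the only cell-assay summary named for comparison, but it is not shown to be the only cellular analysis.

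**Extreme values.** A reader might also infer that the section is wrong to say its summaries limit the influence of extreme values, because a mean does not. That would require the intensity to be an arithmetic mean. The article does not say which mean it is or how values are combined across participants, so this is not part of the point.

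**Illustration.** The threefold difference, the frequencies, the intensities and the SDs are not in the document. Equal brightness makes the gated ratio 1.0 by construction. With 0.5% responders in the control arm, all-cell intensity keeps 47% to 77% power under the assumptions above. This limits the claim to what can happen.

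**What remains.** For flow-based assays the article does not leave the summary open. It names one and says it will be compared. That is a stated choice, and an unseen SAP that used percentages of positive cells would differ from it.

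**Conclusion.** The point holds in a narrow form. For intracellular cytokine staining, the plan's stated comparison is of brightness, whereas the end point is the size of the response. Intensity can therefore miss a real difference in the number of responding cells.

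How much is missed depends on quantities the article does not give. On the assumed 0.05% v 0.15%, a frequency ratio of 3.0 appears as an intensity ratio of 1.0 (gated) or 1.01 to 1.05 (all cells). The loss is smaller with more frequent responders or with brightness that rises with frequency. It would be wrong to conclude that the trial will miss a threefold difference, or that its cellular comparison as a whole is uninformative, because ELISpot is also planned.

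This is a correction worth making but not a threat to the trial. It concerns one assay for an end point that the End Points section lists as secondary, although the Abstract and Anticipated Reporting place cellular responses among the primary end points.

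**What to change.** In Immunogenicity Analysis:

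- For intracellular cytokine staining, make the compared summary the background-subtracted percentage of cytokine-positive CD4+ and CD8+ cells.
- Name the background-subtracted IFN-γ ELISpot count per million PBMCs beside it. The assay is already planned.
- Compare both on a log scale, and state how zero or negative background-subtracted values are handled before logs are taken.
- Keep mean fluorescence intensity as a supportive description, and state the cell population over which it is taken.

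If the SAP already specifies this, aligning the published wording with it is enough. Recruitment and Study Progress reports that laboratory testing is ongoing and statistical analyses are underway. The choice should therefore be dated, with a note of whether it preceded any look at cellular results by arm.

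The cost is a change of wording. Both quantities come from the planned assays, with no further samples or tests.

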### Study Procedures

#### Overview

Briefing sessions containing general information about the study, counseling, and prescreening procedures will be conducted at the trial site clinic and different venues in the community, including open spaces and police or prison facilities. All trial-related activities and vaccinations will take place at the clinical trial sites. Before the study procedures, participants will go through the consent process and will sign 2 copies of the informed consent form. One copy will be kept at the trial site, and the other copy will be provided to the study participant. TANCoV-1.3.20 vaccinations will be administered 4 weeks apart for individuals who will receive the booster dose, and the total follow-up duration will be 6 months. No further vaccinations will be administered in cases of consent withdrawal, confirmed pregnancy, or adverse drug reactions considered possibly related to the study vaccine.

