## Discussion

The COVID-19 pandemic has had a profound impact globally, causing enormous morbidity and mortality while posing unprecedented challenges to economic growth [3]. Rapid vaccine development and an emphasis on mass vaccination have been promising strategies for reducing the severity of the disease as well as minimizing the transmission of the virus. However, there have been some setbacks in the process of vaccination, including, among others, vaccine storage and handling challenges, particularly in low-income countries [32]. In addressing the current gaps and disparities in COVID-19 vaccines among the Global North and South, and as part of preparedness for future pandemics that might require locally developed solutions, several African governments have made efforts in the research and development of locally made solutions, including vaccines. One such endeavor is the production of Tanzania-made COVID-19 vaccines, and TANCoV-1.3.20 is a SARS-CoV-2 vaccine.

As part of the effort to address these setbacks, this clinical trial intends to assess the safety, tolerability, and immunogenicity of TANCoV-1.3.20, a SARS-CoV-2 vaccine, in Tanzania. To assess the potential impact of the vaccine, local, humoral, and cellular immune responses will be measured. Notably, this clinical trial will use TANCoV-1.3.20, a SARS-CoV-2 vaccine that can be administered intranasally, which is a noninvasive mode of administration. Methodologically, in a double-blind manner, some participants will receive the IP intranasally, while the control group will be administered Sinopharm as a standard of care through intramuscular injection. For blinding purposes, normal saline will be given both intranasally and via injection. Methodologically, we anticipate that participants might be hesitant to receive an injection, mainly due to fear associated with the injection and foreign vaccine hesitancy due to myths associated with COVID-19 vaccines. The trial team has a plan to mitigate this by providing education and addressing the fear of needle pricks. In addition, as COVID-19 persists, we anticipate challenges in obtaining COVID-19-negative participants; therefore, a significant number of individuals will need to be screened to identify COVID-19-negative participants.

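### The correlate-of-protection analysis takes infections from the entire study period without limiting them to those after the antibody sample, which biases the association (exploratory analysis, minor)

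*Protocol article*

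**What the plan says.** The Immunogenicity Analysis section states that "correlation analyses, including protection against infection during the entire study period, will be performed to explore the relationship between antibody levels and clinical outcomes". The purpose given is "identifying potential immunological correlates of protection and revealing the predictive value of measured immune parameters".

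The related text is as follows.

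- **Marker.** Immunogenicity Assessment measures "immunoglobulin G (IgG) and immunoglobulin M (IgM) titers using the WANTAI SARS-CoV-2 Ab enzyme-linked immunosorbent assay".
- **Sample times.** Immunogenicity Analysis speaks of "comparing immune responses elicited by the vaccine across study groups and time points" and of models for waning and boosting. It does not say which sample enters the correlate analysis. The only dated immunogenicity reading is in Sample Size Estimation, which sets out to "compare the proportion of seroconversion on day 28".
- **Second dose.** The Study Procedures overview says "TANCoV-1.3.20 vaccinations will be administered 4 weeks apart for individuals who will receive the booster dose". Table 1 places the booster at day 28.
- **Follow-up.** Total follow-up is 6 months.
- **Infection status.** The inclusion criteria ask for negative antigen and antibody tests at entry. No rule covers infection between day 0 and a later blood sample.
- **Circulation.** The Discussion remarks that "as COVID-19 persists, we anticipate challenges in obtaining COVID-19-negative participants".

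**The concern.** A marker can predict an outcome only if it is measured before the outcome occurs. An infection window that covers the whole study, paired with any sample taken after vaccination, takes in infections that came before the sample. Those infections also raise the measured antibody. The affected participants then appear as people with high antibody who were not protected, and this pulls the estimate away from protection whatever the true relation is. The entry tests do not prevent this, because they deal only with infection before enrollment.

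At stake is the reading of the exploratory correlate result for a new vaccine candidate. A protective marker could look weaker than it is or, with a late sample, useless or harmful.

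**Working it through.** **The plan's own figure.** The article gives no figure for this analysis. Its one calculated figure, the sample size, reproduces: (1.645 + 0.842)² × (0.88×0.12 + 0.90×0.10) / (0.90 − 0.88 + 0.20)² = 6.183 × 0.1956 / 0.0484 = 24.98, so 25 per arm and 50 per group. The present point does not depend on it.

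**Inputs.** From the document: 6 months of follow-up (taken as 182 days), day 28 as the one dated reading, and 150 planned participants. Assumed, because the document gives none of these: infections spread evenly over 182 days, attack rate 10-20%, log10 titre SD σ = 0.5, a 4-fold rise after infection (b = log10 4 ≈ 0.6), and a true odds ratio (OR) of 0.5 per log10. The rise is taken either at once or only from 14 days after infection.

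**Formula.** For a roughly normal marker with the same SD in infected and uninfected participants, the log OR per log10 is the difference in means divided by σ². Let f be the share of infections early enough to have raised the sampled titre. The whole-period window adds b × f to the mean of the infected group, so

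log OR(whole period) ≈ log OR(true) + b × f / σ².

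Example, day 28 with no lag: f = 28/182 = 0.154; −0.693 + 0.6 × 0.154 / 0.25 = −0.324; OR = 0.72. The other rows follow in the same way, next to a logistic simulation under the same assumptions.

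| Sample day | f, no lag | OR, formula | OR, simulation | f, 14-day lag | OR, formula | OR, simulation |
|---|---|---|---|---|---|---|
| 28 | 28/182 = 0.154 | 0.72 | 0.73-0.74 | 14/182 = 0.077 | 0.60 | 0.61 |
| 56 | 56/182 = 0.308 | 1.05 | 1.06-1.07 | 42/182 = 0.231 | 0.87 | 0.87-0.89 |
| 90 | 90/182 = 0.495 | 1.64 | 1.60-1.64 | 76/182 = 0.418 | 1.36 | 1.35-1.38 |
| 182 | 1.000 | 5.5 | 5.7-5.8 | 168/182 = 0.923 | 4.6 | 4.6 |

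Counting only infections after the sample, among those not yet infected, gives about 0.5 at each sample day before the end of the study. A month-6 sample has no later infections to predict.

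**Where the sign is lost.** Setting the formula to zero gives f = 0.693 × 0.25 / 0.6 = 0.289. That is a sample at about day 53 without a lag (0.289 × 182) or day 67 with the 14-day lag.

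**No true association.** The whole-period OR is about 1.4 at day 28 without a lag, 1.2 with the lag, and 3.0-3.1 at day 90 without a lag.

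**A second model.** A time-to-infection simulation used N = 150, a true hazard ratio of 0.4 per log10, 10-30% risk, a rise of 0.5-1.0 log10 and a 14-day lag. It compared mean log10 antibody, infected minus uninfected, where negative is the correct sign. Counting only infections after the sample gave −0.23 to −0.26 (days 28 and 56). Counting the whole period gave −0.16 to −0.22 at day 28. At day 56 it gave −0.11 to −0.13 with the smaller rise and about +0.01 with the larger. At month 6 it gave +0.20 to +0.69, with the wrong sign in 96-100% of replicates.

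**Size against noise.** With 150 participants and a 10-20% attack rate there are 15-30 infections. The standard error of the log OR is about 1 / (σ√(N p (1 − p))), which is 1 / (0.5 × √13.5) = 0.54 at 10% and 1 / (0.5 × √24) = 0.41 at 20%. The day-28 bias is log(0.61/0.5) = 0.20 to log(0.74/0.5) = 0.39, so below one standard error. The day-90 bias is log(1.35/0.5) = 0.99 to log(1.6/0.5) = 1.16, about two or more.

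**The case against.** The strongest case against is that the defect is partly inferred. The article never says that infections before the sample count as failures, or that samples taken after infection serve as predictors. The phrase about the entire study period could describe how long infections are watched for. Sample day, risk set and adjustment are commonly left to a full protocol or analysis plan, neither of which is shown. This stands in part: not naming the sample day is no finding. The window, however, is stated, and an analysis plan that adds a sample day while keeping the window would still count earlier infections.

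A reader might infer more than the text supports, in three ways.

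- **That the result will be reversed.** At day 28, the only dated reading, both models show attenuation, and at this trial's size it is smaller than the sampling error. Reversal needs a later sample. Such a sample is plausible but not specified: by Table 1, four of the six arms (4 × 25 = 100 of 150) receive an active dose at day 28, so a sample reflecting their full schedule must come later.
- **That arms are pooled**, so that differences between arms pass for antibody effects. The text mentions no adjustment for arm here, but it does not say that arms are pooled, and the same paragraph plans comparisons across arms.
- **That infections during follow-up will be frequent.** The Discussion remark concerns finding COVID-19-negative participants and gives no rate, so the attack rate used here is an assumption.

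It is also fair that the analysis is exploratory by its own wording and does not appear among the listed objectives or end points.

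**Conclusion.** The concern holds in limited form. The stated window does not require infection to follow the antibody sample, and followed as written it biases the association in a known direction, away from protection. Under the assumed inputs, a true OR of 0.5 per log10 is weakened with a day-28 sample, roughly lost at day 56 and reversed only with later samples. These sizes rest on assumed incidence, titre spread and antibody rise, and above all on a sample day that the article does not fix. The direction needs only that infection raises the measured antibody.

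Severity is minor. No safety or seroconversion conclusion depends on this analysis, and the documents do not support reading it as a threat to the trial's main results.

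**What to change.** Replace the whole-study window with a landmark rule. Relate the antibody value at a fixed, named visit only to first infections after that visit, among participants not infected by then. Alternatively, use antibody as a time-updated covariate, taking only samples collected before infection. Stratifying or adjusting by arm is a sensible addition. Record the rule before antibody values are linked to infections; the article says that outcomes will be analyzed once follow-up visits and assays are complete.

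The cost is wording only, with the same samples and tests. Infections before the landmark leave this analysis: 28/182, about 15%, for day 28 under even incidence, or roughly 2 to 5 of the assumed 15 to 30. With precision driven by the number of infections, the standard error grows by about 1/√(1 − 0.154) = 1.09, or 9%. A later landmark costs more: 56/182, about 31%, at day 56.
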